#### Efficacy evaluation

2.5.2

Refer to “Guidelines for Clinical Research of New Chinese Medicine”. Efficacy was evaluated by the ratio of the difference between the points before and after treatment compared to the points before treatment. Syndrome treatment efficiency = (total points before treatment total points after treatment)/total points before treatment × 100%.

1.Clinical control: clinical symptoms and signs disappeared or basically disappeared, and syndrome scores were reduced by ≥95%;2.Significant effect: clinical symptoms and signs were significantly improved, and syndrome scores were reduced by 70%;3.The signs and symptoms have improved, and the syndrome scores have decreased by ≥30%;4.Ineffective: the clinical symptoms and signs have not improved significantly, and the syndrome scores have decreased by less than 30%.

### Sample size calculation

2.6

With reference to previous clinical trials on the application of thunder-fire moxibustion combined with acupressure in the treatment of OMS, the standard deviation was 3.13. The purpose of this trial was to observe the difference in relief of ocular muscle spasm between patients with conventional thunder-fire moxibustion and acupressure. We expect that the treatment group can cause 90% of the changes to be clinically meaningful, in line with the superior effect design of the measurement data, and the sample size formula of the measurement index is as follows: 

. Combined with clinical practice, α = 0.05, β = 0.2, and the table *f* (*α*, *β*) = 7.9 then the calculated sample size is 33 cases in each group. According to the 15% shedding rate, the sample size in each group is 38 cases, and the treatment group and the control group total 76 cases.

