#### Primary outcome measures

2.5.1

We will formulate standards for evaluating the efficacy of OMS in accordance with the Standards for Diagnosis and Treatment of Traditional Chinese Medical Diseases. The specific evaluation criteria for the efficacy are as follows:

1.Cure: the twitching of the eye cells or facial muscles disappears without recurrence within half a year;2.Effective: the spasm level of the eye cells or facial muscles is reduced, the number of twitching is reduced, and the time between twitching is shortened;3.Ineffective: The degree of spasm of the ocular muscles has not improved. All patients were graded according to the degree of blepharospasm. Level 0 is without spasm. Level 1 is an increase in convulsions caused by external stimuli. Grade 2 is mild spasm, slight twitching of eyelids, and no dysfunction. Grade 3 is moderate spasm, with obvious eyelid spasm and mild dysfunction. Grade 4 is severe spasm, severe blepharospasm, obvious dysfunction, affecting work and life.

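### The 33 per group and 80% power are calculated for a continuous variable with SD 3.13, but the declared primary outcome is a three-category rating, so the stated power does not apply to it.

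*Protocol article*

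**What the plan says.** Protocol article, 2.5.1 (Primary outcome measures), defines three ordered categories. The best is "Cure: the twitching of the eye cells or facial muscles disappears without recurrence within half a year" and the worst is "Ineffective: The degree of spasm of the ocular muscles has not improved". The same section describes a spasm grade running from "Level 0 is without spasm" to "Grade 4 is severe spasm, severe blepharospasm, obvious dysfunction, affecting work and life".

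Section 2.5.2 (Efficacy evaluation) defines a syndrome total score before and after treatment. It turns the percentage reduction into four response categories. It carries neither a primary nor a secondary label.

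Section 2.6 (Sample size calculation) describes the sizing as "in line with the superior effect design of the measurement data, and the sample size formula of the measurement index". Its inputs are SD 3.13, α = 0.05, β = 0.2 and f(α, β) = 7.9, "then the calculated sample size is 33 cases in each group". A 15% allowance for dropout raises this to 38 per group and 76 in total. The variable with SD 3.13 is not named.

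Section 2.8 (Statistical analysis) treats continuous and count data separately. It plans independent-sample t tests for between-group differences in efficacy, and chi-square or non-parametric tests for count data. It does not say which of these is the primary comparison.

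**The concern.** A sample size calculation tells the reader which difference, on which variable, the trial can reliably detect. Here the calculation and the declared primary outcome are different kinds of variable. The protocol draws the same line itself in 2.8, where means and SDs go with one type of data and proportions with the other.

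If the 80% is read as the power of the primary comparison, a non-significant result on the cure/effective/ineffective rating would be given a weight that the calculation does not support. The control group receives thunder-fire moxibustion, so the question is what acupressure adds to a treatment already given, and it matters what size of added effect the trial can see.

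**Working it through.** **Inputs from section 2.6.** SD = 3.13; α = 0.05; β = 0.2; f = 7.9; n = 33 per group; dropout 15%.

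**1. The plan's own figures.**
- Two-sided f = (1.96 + 0.84)² ≈ 7.85, which agrees with 7.9. One-sided f would be 6.18.
- Dropout: 33 × 1.15 = 37.95, so 38 per group and 76 in total, as stated.
- The formula is not legible in the text available, so 33 cannot be rebuilt forwards. The usual two-means formula n = 2·f·SD²/δ² can be solved backwards: δ = √(2 × 7.9 × 3.13² / 33) = √(154.8 / 33) = 2.17 points. In SD units this is 2.17 / 3.13 = 0.69.

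So 33 per group gives 80% power for a continuous variable with SD 3.13 and a true difference of about 2.17 points.

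**2. Can SD 3.13 belong to anything in 2.5.1?** The SD of a bounded variable is at most half its range.
- Three-level rating scored 0, 1, 2: maximum SD 2/2 = 1.
- Spasm grade 0 to 4: maximum SD 4/2 = 2.00 (2.03 as a sample SD with 33 patients).
- Change in grade, −4 to +4: the cap is 4, so 3.13 is not strictly impossible. It requires a range of at least 2 × 3.13 = 6.26, that is, seven grades. Some patients would have to worsen by three or more grades while others improve by three or more, in large numbers on both sides. That is not credible.

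**3. Is there another candidate?** The syndrome total score in 2.5.2 could have SD 3.13. The document does not say so and does not make that score primary.

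**4. What 33 per group gives on the rating.** The protocol states no category or response rates, so every rate below is an assumption. All tests are two-sided at 5%.

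*(a) Three ordered categories.* The 0.69 SD shift was applied to a latent normal variable cut into three categories, with 20,000 simulated trials for each control distribution:

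| Control: cure / effective / ineffective | Wilcoxon | 3×2 chi-square |
|---|---|---|
| 10 / 40 / 50% | 70% | 59% |
| 20 / 50 / 30% | 70% | 60% |
| 30 / 50 / 20% | 68% | 58% |
| 10 / 60 / 30% | 68% | 57% |
| 33 / 34 / 33% | 68% | 59% |
| 5 / 65 / 30% | 64% | 52% |
| 5 / 80 / 15% | 55% | 42% |

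*(b) Cure plus effective counted as success.* Power = Φ{[(p₂ − p₁) − 1.96·√(2p̄(1 − p̄)/n)] / √[(p₁(1 − p₁) + p₂(1 − p₂))/n]}, with p̄ the mean of the two rates.
- 60% v 90%: (0.300 − 0.209) / 0.100 = 0.91, power 82%.
- 70% v 90%: (0.200 − 0.193) / 0.095 = 0.07, power 53%. For 80% power, 62 per group would be needed.
- 80% v 90%: (0.100 − 0.172) / 0.087 = −0.83, power 20%.

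**The case against.** The strongest defence is that the sizing does match a planned analysis. Section 2.5.2 supplies a total score, 2.8 plans a t test for differences in efficacy, and 2.6 speaks of relief of spasm without using the words primary comparison. On that reading the power calculation is sound and the primary label sits on the wrong endpoint. This is plausible, and it shapes the first option under the fix. It does not remove the contradiction: 2.5.1 is the only section headed as primary, the score in 2.5.2 has no such label and is itself cut into four categories, and a t test does not give a three-level rating an SD of 3.13.

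It is also fair to say that the calculations in step 4 depend on choices the protocol does not make. It never combines cure and effective into a success, and doing so discards information. The ordinal test loses less.

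Four stronger readings are tempting but not supported:
- **That the trial is shown to be underpowered.** Without category rates, the power on the rating could be above or below 80%.
- **That no difference to detect is stated.** The formula is not legible in the text available, and the difference may have stood there. The 90% mentioned in 2.6 does not lead to 33 if read as a difference: 0.9 points gives about 191 per group with f = 7.9, and 0.9 SD gives about 20. That is no proof that the difference was omitted.
- **That 2.17 points is more than half the 0 to 4 grade range, and so implausibly large.** If SD 3.13 cannot be the SD of the grade, 2.17 points is not on that scale and the comparison has no meaning.
- **That 2.6 sizes a different contrast.** Its wording, "between patients with conventional thunder-fire moxibustion and acupressure", is loose, but the abstract and section 2.4 make clear that the combination is compared with moxibustion alone.

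**Conclusion.** The mismatch stands on the document's own text. The 80% power belongs to an unnamed continuous variable with SD 3.13 and does not carry over to the cure/effective/ineffective rating declared primary. The fault is in the match between endpoint and calculation, not in the arithmetic: f and the dropout step agree with the stated inputs.

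The size of the discrepancy is uncertain. If the effect that 33 per group was built to detect is seen only through three ordered categories, power falls from 80% to about 55% to 70% by Wilcoxon under the control distributions tried. On a success/failure reading, 80% power needs a difference of about 60% v 90%. These figures assume 33 evaluable patients per group, a two-sided 5% test, the usual two-means formula for the back-calculation, and the rates and latent shift shown. They illustrate the issue and do not estimate the trial's true power.

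**What to change.** Make the primary outcome and the calculation refer to the same variable, in one of two ways.

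- **(a) Make the continuous score primary.** Name the variable with SD 3.13 as the single primary outcome (the syndrome total score, if that is its source). State its range, where the SD comes from and the difference used, and test it with the mean comparison already planned in 2.8. With SD 3.13, 33 per group corresponds to about 2.17 points. That value needs its own clinical justification and should not be adopted because it fits the sample size.
- **(b) Keep the three-category rating as primary.** Replace the 80% claim with the power or detectable difference on that rating at 33 per group. State the assumed category or response rates, and name the ordinal or two-proportion test.

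Either option is a rewording of 2.6, with 2.5.1 also changed under (a), and neither adds patients. The cost of (a) is that the categorical rating gives up its primary status. The cost of (b) is that the stated power may be less favourable than 80%, depending on the rates assumed.

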### Randomization and blinding

2.7

The random method will use the closed envelope method for block randomization. Use the SAS software PROC PLAN procedure statement for random grouping. The subjects will be numbered 1 to 76 according to the order in which the patients were enrolled, and random numbers and assignments corresponding to the order of inclusion were obtained. The groups will be sealed in opaque envelopes, and the order of inclusion will be affixed to the surface of the envelopes. Randomization envelopes and distributions are performed by individuals who are not involved in treatment and evaluation.

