### Statistical analysis

2.8

According to the m-ITT principle, all randomized cases will be included. And there is at least 1 treatment and 1 post-baseline data. The missing data are not filled, and the actual observation values are used for statistical analysis. The measurement data are described by mean, standard deviation, median, and quartile. If the data meets the normal distribution, it is compared with the baseline value at the time of enrollment, and a paired T test is used. Differences in efficacy between the 2 groups will be compared using independent sample *t* tests. If the normal distribution is not satisfied, a non-parametric test is used. The count data is described using a composition ratio. If the normal distribution is satisfied, the changes before and after treatment in the 2 groups are tested by X^2^. If the normal distribution is not satisfied, a non-parametric test is used. The statistical software is SPSS 24.0, when *P* < .05, it showed that the difference is statistically significant.

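### The 38 per group in section 2.6 does not retain the stated 33 at the stated 15% dropout; 38 covers about 13%, and 15% would need 39

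*Protocol article*

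**What the plan says.** Section 2.6 of the protocol article sets the error rates ("α = 0.05, β = 0.2, and the table" value f = 7.9) and cites previous trials for the spread ("the standard deviation was 3.13"). It then gives the result: "then the calculated sample size is 33 cases in each group". The dropout step follows at once: "According to the 15% shedding rate, the sample size in each group is 38 cases". Both arms together make 76. No formula is printed for the step from 33 to 38.

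The total is carried into section 2.3 (76 patients to be selected) and into the envelope numbering in section 2.7: "The subjects will be numbered 1 to 76 according to the order in which the patients were enrolled".

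Section 2.8 defines a modified intention-to-treat set, which requires at least one treatment and one post-baseline value. On missing values it says: "The missing data are not filled, and the actual observation values are used for statistical analysis".

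**The concern.** A dropout allowance is meant to ensure that the required number remains after the expected share of enrolled patients has been lost. The required number is therefore divided by the retained fraction. Adding 15% of the required number gives a smaller figure, because the loss then falls on a larger base than the one used to compute the allowance. The printed 38 looks like the result of adding.

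What is at stake is whether the enrolment target delivers the plan's own requirement under the plan's own assumption. Missing values are not imputed, so a patient without the outcome is not made up for in the analysis. A size rounded to just meet 80% power also leaves little slack.

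**Working it through.** **Inputs, all from section 2.6:** 33 per group before dropout; dropout 15%; 38 per group and 76 in total after the allowance; α = 0.05; β = 0.2; f = 7.9; standard deviation 3.13. The section's equation is missing from the text at hand and no planned difference can be read there. The 33 is therefore taken as given. The dropout step does not need the difference.

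**1. Reproducing the plan's figure.** 33 × 1.15 = 37.95, rounded up to 38. This matches the printed number.

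**2. The usual allowance.** 33 / (1 − 0.15) = 33 / 0.85 = 38.82, rounded up to 39 per group, 78 in total.

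**3. What each size leaves after 15% loss.**

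| Enrolled per group | Left after 15% loss | Stated requirement |
|---|---|---|
| 38 | 38 × 0.85 = 32.3 | 33 |
| 39 | 39 × 0.85 = 33.15 | 33 |

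**4. The dropout that 38 does cover.** 1 − 33/38 = 5/38 = 13.2%. A sixth loss (6/38 = 15.8%) leaves 32.

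**5. What this does to power.** For two-sided 5% and 80% power, (1.960 + 0.842)² = 7.85, in line with the plan's 7.9. A one-sided 5% would give 6.18. The comparison is therefore treated as two-sided.

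With the usual formula n₀ = 2f·SD²/δ², where n₀ is the requirement before rounding, the standardised difference is √(2 × 7.9 / n₀). Power at n per group is then Φ(√(7.9 × n/n₀) − 1.96). Because δ cannot be read, n₀ is an assumption. If 33 was rounded up, n₀ lies above 32 and at most 33.

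| Assumed n₀ | Standardised difference | Power at n = 32.3 |
|---|---|---|
| 32.0 (lower limit) | 0.703 | 80.6% |
| 32.3 | 0.699 | 80.2% |
| 32.5 | 0.697 | 80.0% |
| 33.0 | 0.692 | 79.4% |

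For n₀ = 33.0, the same formula gives 80.3% at 33 per group, so the 15% loss costs about 0.9 percentage points in that case. With 32 whole patients per group, power runs from 79.0% (n₀ = 33) to 80.3% (n₀ = 32).

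**The case against.** **The power shortfall is not established.** A reader might infer that the trial falls below its 80% target, at 79%. That figure requires an unrounded requirement of exactly 33.0, the least favourable value if 33 was rounded up. For about half of the possible range (n₀ up to 32.5), the plan's formula still gives 80% or more at 32.3 per group. This objection stands. A t-test calculation does not rescue the stronger reading. With n₀ = 33 it gives about 78% at 32.3 but only about 79% at the full 33, so roughly half of its distance from 80% would remain with no loss below 33.

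**The route to 38 is inferred.** A reader might also take it as shown that the requirement was multiplied by 1.15. The article prints no inflation formula. An unrounded requirement of up to 32.3 divided by 0.85 also gives at most 38. Multiplication remains the likelier route, because the text carries 33 forward and 33 × 1.15 rounds up to exactly 38. By either route, 38 less 15% is fewer than the stated 33.

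**Dropping out need not mean leaving the analysis.** Section 2.8 keeps a treated patient who has one post-baseline value, and treatment is a single 10-day course. Some dropouts may therefore still be analysed. This stands in part. The cure category in section 2.5.1 requires half a year without recurrence, which one early value cannot establish, and nothing is imputed. The plan also treats the 15% as a loss to be made up, since it enlarges the sample for it.

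**The gap is small against the uncertainty of a planning guess.** This is fair, since 13.2% and 15% are close. It limits the weight of the point but does not make the printed figures agree.

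**Conclusion.** The point holds as a minor arithmetic inconsistency. Section 2.6 states 33 needed, 15% lost and 38 enrolled per group, and these cannot all be right together: 38 less 15% is 32.3. The shortfall is 0.7 of a patient per group. The whole-number correction is one more per group, two in total.

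The inconsistency itself rests only on printed figures. The size of its effect on power does not. About 79% to 81% at 15% loss assumes a two-sided test, the usual two-mean formula and a requirement rounded up to 33. The documents do not support a claim that power misses 80%, or that the design is undermined.

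**What to change.** Restate the dropout sentence in section 2.6, for example: *With 38 patients per group (76 in total), the required 33 per group are retained if dropout does not exceed about 13%; a dropout of 15% would leave about 32 per group.* This costs one sentence, with no extra patients and no change to the envelopes.

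If the sponsor prefers to keep the 15% allowance, the matching size is 39 per group, 78 in total. The totals in sections 2.3 and 2.6 and the numbering in section 2.7 would then change to 78, at the cost of two more patients.

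In either case, print the inflation formula used. Do not insert a single power figure such as 79% unless it is recomputed from the sponsor's own planned difference.

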### Randomization and blinding

2.7

The random method will use the closed envelope method for block randomization. Use the SAS software PROC PLAN procedure statement for random grouping. The subjects will be numbered 1 to 76 according to the order in which the patients were enrolled, and random numbers and assignments corresponding to the order of inclusion were obtained. The groups will be sealed in opaque envelopes, and the order of inclusion will be affixed to the surface of the envelopes. Randomization envelopes and distributions are performed by individuals who are not involved in treatment and evaluation.

### Statistical analysis

2.8

According to the m-ITT principle, all randomized cases will be included. And there is at least 1 treatment and 1 post-baseline data. The missing data are not filled, and the actual observation values are used for statistical analysis. The measurement data are described by mean, standard deviation, median, and quartile. If the data meets the normal distribution, it is compared with the baseline value at the time of enrollment, and a paired T test is used. Differences in efficacy between the 2 groups will be compared using independent sample *t* tests. If the normal distribution is not satisfied, a non-parametric test is used. The count data is described using a composition ratio. If the normal distribution is satisfied, the changes before and after treatment in the 2 groups are tested by X^2^. If the normal distribution is not satisfied, a non-parametric test is used. The statistical software is SPSS 24.0, when *P* < .05, it showed that the difference is statistically significant.

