#### Criteria for termination of trials

2.3.4

If the following happens, we will terminate the test. Severe acute disease response; severe allergic reactions and other adverse reactions; those who withdraw due to worsening or ineffective eye disease during treatment

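### Observed-case analysis with a post-baseline requirement lets patients who withdraw for worsening, inefficacy or adverse reaction, and have no recorded grade, leave the primary denominator

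*Protocol article*

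**What the plan says.** All references are to the protocol article.

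- **Statistical analysis (2.8), analysis set:** "According to the m-ITT principle, all randomized cases will be included. And there is at least 1 treatment and 1 post-baseline data". The first sentence takes in everyone randomized; the second limits the set to patients with treatment and a post-baseline value.
- **Statistical analysis (2.8), missing data:** "The missing data are not filled, and the actual observation values are used for statistical analysis". This is a stated choice of observed-case analysis.
- **Criteria for termination of trials (2.3.4):** the listed reasons include severe allergic and other adverse reactions, and "those who withdraw due to worsening or ineffective eye disease during treatment".
- **Primary outcome measures (2.5.1):** three categories. The best is "Cure: the twitching of the eye cells or facial muscles disappears without recurrence within half a year". The failure category reads "The degree of spasm of the ocular muscles has not improved", so it rests on an observed degree of spasm. The section does not mention patients who stop early.
- **Sample size calculation (2.6):** "then the calculated sample size is 33 cases in each group", and then "According to the 15% shedding rate, the sample size in each group is 38 cases".

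**The concern.** For a Cure/Effective/Ineffective outcome, a patient who leaves because the condition worsened or treatment did not work has in effect supplied the outcome. Treating that patient as missing, and then analysing observed values only, removes a known failure from the denominator. The missingness is caused by the outcome, so it cannot be ignored.

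Two things are at stake. The success rate in each arm is overstated. The comparison between arms is also biased if failure-driven withdrawal is unequal, and the bias favours the arm that loses more failures. It could create a false benefit for added acupressure or hide a real one. Unequal withdrawal is possible: the trial is only single-blinded, and patients can feel whether pressure is applied. The documents do not show that it will happen.

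The statement that all randomized cases are included adds to the problem, because a reader of the results would take the denominator to be everyone randomized.

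**Working it through.** **1. The plan's own allowance for loss.** Inputs from section 2.6: 33 per group before loss, 15% loss, 38 per group after.
- 33 × 1.15 = 37.95, rounded up to 38. This reproduces the plan's figure. (33 / 0.85 = 38.8, or 39, is the alternative convention; the one-patient gap does not matter here.)
- Expected loss per group: 38 × 0.15 = 5.7, about 6 patients. The plan does not say why they would be lost.

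**2. Who leaves the denominator under section 2.8.**

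| Patient | In the set? | Counted as Ineffective? |
|---|---|---|
| Withdraws for worsening or inefficacy, post-baseline grade recorded | Yes | Yes, if that grade shows no improvement |
| Withdraws for worsening, inefficacy or adverse reaction, no post-baseline grade | No | No |
| Lost for an unrelated reason, no post-baseline grade | No | No (outcome unknown) |

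The problem lies in the second row.

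**3. Size in counts, as an illustration.** Assume 23 of 38 patients (60.5%) are true successes in each arm and all withdrawals are failures without a grade.
- Six leave one arm and none the other: 23/32 = 71.9% v 23/38 = 60.5%, a false difference of 11.3 points (unrounded arithmetic).
- With 19 or 27 true successes instead: 19/32 − 19/38 = 9.4 points; 27/32 − 27/38 = 13.3 points.
- Six leave each arm: 71.9% v 71.9%. There is no false difference, but both rates are too high.
- Failures kept in the denominator: 23/38 in both arms, difference 0 in every case.

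**4. Size as error rates.** Assumptions, none of them given in the documents: true success p = 60% in both arms; success means Cure or Effective; all withdrawals are failures and all are excluded; 38 per arm; Pearson chi-square at 5%. With a fraction w withdrawn, the observed success rate is p / (1 − w). Type I error comes from simulation (400,000 trials per row).

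| Withdrawal, arm v arm | Observed success | Type I error, observed cases | Type I error, withdrawals counted Ineffective |
|---|---|---|---|
| 15% v 5% | 0.60/0.85 = 70.6% v 0.60/0.95 = 63.2% | about 10% | about 5% |
| 25% v 5% (averages 15%) | 0.60/0.75 = 80.0% v 63.2% | about 32% | about 5% |
| 15% v 15% | 70.6% v 70.6% | about 5% | about 5% |

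**5. Sensitivity to the worst-case assumption.** If only half of the failure withdrawals lack a grade and leave the set, the 15% v 5% case becomes 7.5% v 2.5% excluded. Observed success is 0.60/0.925 = 64.9% v 0.60/0.975 = 61.5%, and type I error is about 6%. For 25% v 5% it is about 10%.

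**6. The bias can also hide a benefit.** Take true success of 60% (15% withdrawn) v 75% (5% withdrawn). Observed-case analysis shows 0.75/0.95 − 0.60/0.85 = 8.4 points instead of 15. Power falls from about 29% to about 13%.

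**The case against.** The strongest objection is to a reading that the text invites: that section 2.8 removes every patient who withdraws because treatment failed. The documents do not support that. Section 2.8 excludes only patients without treatment and a post-baseline value. Section 2.3.4 speaks of withdrawal during treatment, and a judgement of worsening or inefficacy implies that someone looked at the patient. If a grade was recorded, the patient stays in, and the Ineffective category fits. Declining to impute does not discard a recorded failure. The visit schedule and the flow chart are figures that are not shown, so an assessment at withdrawal may exist. This part of the objection stands, and it confines the point to patients without a recorded grade.

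A reader might also take the 10% or 32% error rates as what this trial would show. They are worst-case illustrations. The article gives no success rates, no split of withdrawals and no reasons for the 15% loss. Its exclusion criteria mention loss to follow-up from changes in working environment, which has nothing to do with efficacy. With equal withdrawal the test remains valid. This stands too.

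A third objection is that the classification of withdrawn patients could sit in an analysis plan that is not shown. That would excuse silence. Here, however, the article makes a positive choice not to fill missing data, and it describes an analysis set in two sentences that conflict. Those statements can be judged as written.

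Finally, counting everyone without a post-baseline value as Ineffective would cover patients who were never treated or who left for unrelated reasons. The argument that the outcome is known does not reach them, so that convention belongs in a sensitivity analysis.

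**Conclusion.** The concern holds in a limited form. Section 2.8 lets patients who withdraw for worsening, inefficacy or adverse reaction, and who have no recorded post-baseline grade, leave the primary denominator, although the section says that all randomized cases are included. Success rates are then overstated, and the treatment comparison is biased if such withdrawals are unequal between arms. The direction cannot be known in advance.

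The size depends on three assumptions outside the documents: the true success rate, the share of withdrawals that are ungraded failures, and the imbalance between arms. At 60% true success with all withdrawals ungraded failures, 15% v 5% gives a false difference of 7.4 points (70.6 − 63.2) and a type I error of about 10%. If half of them are graded, type I error is about 6%. With equal withdrawal it is about 5%, with both rates inflated.

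This should be fixed because it touches the primary comparison and the remedy is cheap. It does not show that the trial's conclusion would be wrong.

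**What to change.** In section 2.8, for the primary Cure/Effective/Ineffective outcome:

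1. Analyse all randomized patients in the group to which they were assigned.
2. Count withdrawal for worsening, inefficacy or adverse reaction as Ineffective.
3. Report the observed-case (m-ITT) analysis as a sensitivity analysis.
4. For patients missing for unrelated reasons, name a sensitivity analysis in advance, for example with missing counted as Ineffective.
5. Reword the analysis-set sentences so that the m-ITT set is no longer described as including all randomized cases.

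The rule should be fixed before outcome data are seen, since a later choice could be made knowing which arm it favours. The cost is a few sentences, one extra table and slightly lower reported success rates. The sample size, visits and treatment need not change for this point.

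### Section 2.8 compares the groups on the syndrome score without baseline adjustment, although baseline is collected; ANCOVA would usually be more precise, and the within-group paired tests should be descriptive

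*Protocol article*

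**What the plan says.** Section 2.8 (Statistical analysis) gives two tests for measurement data. Within each group, if the data are normal, "it is compared with the baseline value at the time of enrollment, and a paired T test is used". Between groups, "Differences in efficacy between the 2 groups will be compared using independent sample" *t* tests. If normality is not met, a non-parametric test replaces the planned one. Significance is P < .05 throughout, and the tests are not ranked. For count data, "the changes before and after treatment in the 2 groups are tested by X"² (chi-squared), again with a non-parametric alternative.

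Section 2.5.2 (Efficacy evaluation) defines the score measure: "Efficacy was evaluated by the ratio of the difference between the points before and after treatment compared to the points before treatment". That percentage is then used to place patients in four response bands.

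Section 2.5.1 (Primary outcome measures) is different in kind. It has three ordered categories, the best of which requires that "the twitching of the eye cells or facial muscles disappears without recurrence within half a year", together with a spasm grade from 0 to 4.

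Section 2.6 (Sample size calculation) uses a formula for measurement data. It states that "the standard deviation was 3.13", with "α = 0.05, β = 0.2" and 33 patients per group before dropout.

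**The concern.** Both the percentage in section 2.5.2 and the paired test in section 2.8 need a pre-treatment score, so that score will exist. The between-group test as written does not use it as a covariate. With about 33 evaluable patients per group, this may cost useful precision on the kind of outcome for which the trial was sized.

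Two further features of section 2.8 add to this:

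- **Paired tests.** A before-after test within one group does not estimate what acupressure adds. Both groups receive thunder-fire moxibustion (section 2.4), and the diagnostic criteria describe spasm that varies with fatigue and nervousness (section 2.3.1). Improvement over 10 days could therefore appear in both groups whether or not acupressure contributes. One significant and one non-significant paired test could be misread as a difference between groups.
- **Normality switch.** When the main test is chosen after looking at the data, the reported effect (a mean difference or a rank comparison) is not fixed in advance.

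**Working it through.** **Inputs from the documents.** SD 3.13, α 0.05, β 0.2, f(α, β) 7.9 and 33 per group (section 2.6). The section does not say whether 3.13 is the SD of the final score, the change or the percentage change.

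**Inputs that are assumed.** The correlation *r* between baseline and post-treatment score is not given, so a range is used. Equal SDs at baseline and after treatment are assumed.

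**Step 1: the plan's own figure.** The 33 per group cannot be reproduced forward, because no mean difference in score units is stated and the formula is not legible. Solving the usual two-mean formula n = 2·SD²·f/δ² backward gives δ = √(2 × 3.13² × 7.9 / 33) = 2.17, or 2.17/3.13 = 0.69 SD. This value is implied by n = 33 and is not in the protocol. A *t* test must therefore show about 80% power against it, and it serves only as a common yardstick below.

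**Step 2: variance of the treatment difference.**

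- ANCOVA relative to a post-score *t* test: 1 − r².
- ANCOVA relative to a change-score *t* test: (1 − r²) / [2(1 − r)] = (1 + r)/2.

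| Assumed r | 1 − r² | Reduction v post score | (1 + r)/2 | Reduction v change score |
|---|---|---|---|---|
| 0.3 | 0.91 | 9% | 0.65 | 35% |
| 0.5 | 0.75 | 25% | 0.75 | 25% |
| 0.7 | 0.51 | 49% | 0.85 | 15% |

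**Step 3: power at 33 per group, δ = 2.17 (normal approximation).**

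- If 3.13 is the SD of the final score, ANCOVA has 80%, 84%, 90% and 98% power at r = 0, 0.3, 0.5 and 0.7, against 80% for a post-score *t* test.
- If 3.13 is the SD of change, ANCOVA has 94%, 90% and 86% at r = 0.3, 0.5 and 0.7, against 80% for a change-score *t* test.

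**Step 4: the price of the covariate.** One degree of freedom is lost. At r = 0 with 33 per group, exact power moves from 79.05% (64 df) to 79.04% (63 df), which is negligible.

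**Step 5: against percentage change.** This has no simple formula, so it was simulated at 33 per group.

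- *Additive effect* (δ = 2.17, SD 3.13, assumed baseline mean 10 to 20, r from 0 to 0.7; 3,000 trials per scenario): the *t* test on percentage change had 54% to 97% power and ANCOVA 78% to 97%. ANCOVA was higher in every scenario, by about 1 to 24 points. With mean 10 and r = 0.3 it was 70% v 82%; with mean 20 and r = 0.7 it was 96.5% v 97.4%.
- *Proportional effect* (assumed mean reductions 40% v 54%, SD 20 percentage points, baseline mean 10 with coefficient of variation 0.2 to 0.45; 4,000 trials per scenario): the order reversed. Percentage change had 79% to 80% power and ANCOVA on the raw score 72% to 77%.

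**The case against.** The strongest reply is that an unadjusted two-sample comparison in a randomised trial is valid. Chance baseline imbalance is already covered by its error rate, and covariates are commonly left to an analysis plan that is not shown. The first part stands: this is a matter of efficiency, not of bias. The second has limited force, because the article does not leave the test open. Section 2.8 names it, so the point concerns what is written.

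Four stronger readings are tempting, and the documents do not support them.

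- **That percentage change is what the *t* test analyses.** Section 2.8 speaks only of efficacy differences. Section 2.5.2 uses the percentage to assign response bands, which are count data and would go to chi-squared or a non-parametric test. The *t* test could equally be on post-treatment points or simple change. Criticism of the ratio itself, such as skew or the weight of low-baseline patients, also lacks support, because no score range or distribution is given.
- **That ANCOVA always gives more power.** The gain depends on an unstated correlation, is nil against a post-score test near r = 0, and can reverse against percentage change when the effect is proportional to baseline.
- **That the paired tests will be used to claim efficacy.** Section 2.8 assigns the between-group question to the independent-sample test. The paired tests carry a risk of misreading and are not a stated efficacy criterion.
- **That ANCOVA would repair the primary outcome.** Cure, effective and ineffective are categories, to which linear ANCOVA does not apply.

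**Conclusion.** The point holds in a limited form. For the syndrome score, section 2.8 fixes a between-group test without baseline adjustment, leaves its variable unnamed, lets a normality check choose the test, and sets within-group paired tests beside it without ranking them. Baseline-adjusted ANCOVA is, apart from a negligible loss of one degree of freedom, at least as precise as a *t* test on the post-treatment score or on simple change. The variance reduction is 9% to 49% against the former and 15% to 35% against the latter, over assumed correlations of 0.3 to 0.7 with equal SDs. Against percentage change the advantage depends on the form of the effect and is not guaranteed. The power figures rest on a difference solved back from n = 33 and illustrate scale only. The planned test remains valid, so this is a recommended improvement, not an error that would invalidate the trial.

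**What to change.** In section 2.8, for the syndrome score only:

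1. Name the variable and the test: post-treatment total points, analysed by ANCOVA with treatment as factor and baseline points as covariate. Report the adjusted mean difference with its 95% CI.
2. State that this between-group comparison is the efficacy test for the score, and that within-group paired comparisons are descriptive.
3. Replace the normality-driven switch with a rank-based ANCOVA, pre-specified as a sensitivity analysis.
4. If the team expects the effect to be proportional to baseline, say so and justify the scale of analysis before any outcome data are seen.

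The categorical primary outcome in section 2.5.1 keeps its own between-group categorical or ordinal test.

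The cost is a rewording of section 2.8. No new data, visits or patients are needed, because the baseline score is already required by section 2.5.2.
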